### Sample size calculation

Given a prevalence of psychosocial risk factors (depression, anxiety or both) in HF patients from general practices of 20% [6] and a recognition rate of 75% [20], we aim for a sample that provides us a minimum power of 80% to detect a minimum difference of at least any 5 points on the EQ-5D visual analogue scale (EQ-VAS) [42] with α = 0.05. Therefore, a sample of 672 participants with depression and/or anxiety is needed, of whom 504 have depression and/or anxiety recognized by their GP (P+/+) and 168 with depression and/or anxiety not recognized by their GP (P+/−).

Given an estimated participation rate of 40%, a return rate of the baseline questionnaire of 90% and a loss to follow-up rate of 15% a total of 10,973 patients with heart failure are needed to be invited into the study by their GP (see Figure 2).

**Figure 2 F2:**
[figure not shown]
Sample size considerations.

For a comparison with heart failure patients without psychosocial risk factors, a random sample of N = 2,370 of those who completed the baseline questionnaire but were not identified to have depression and/or anxiety will be drawn (P−/−). Taking a loss to follow-up rate of 15% into account, a total of 2,015 patients with heart failure but without depression and/or anxiety at baseline will be included in the analyses. A minimum number of 118 patients at the follow-up assessment would already provide a power of 80% to detect differences between the groups (P+/+, P+/− and P−/−) of at least any 5 points on the EQ-5D visual analogue scale (EQ-VAS) [42] with α = 0.05.

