### Quality assurance

The study is centrally coordinated by the study center Hamburg. All processes regarding the recruitment of GP practices and patients will be parallelized between both recruiting centers. To avoid selection bias, patients with heart failure are selected electronically from the medical records. We use validated instruments for the assessment of baseline and follow-up characteristics. All study staff conducting telephone interviews have been trained. All interviewers are blind regarding the group the patient has been allocated to.

For the data collection from GPs, depression and anxiety is offered in a full list of other potential comorbidities to minimise social desirability bias and to mask the focus on anxiety and depression. Additionally, the GP is interviewed regarding patients with and without depression and/or anxiety. The 75% of eligible patients in the observation group 3 exceed the number required by the power calculation and are suggested to be sufficient to detract from the focus on patients with depression and anxiety. Questionnaires are electronically imported into the database. All import data is double-checked before analysis. Analyses are performed anonymously.

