### Data analysis

The prevalence of comorbidities in patients with HF and difficulties in the treatment of patients with HF will be analyzed by descriptive statistics. The prevalence of recognition/non-recognition of psychosocial risk factors in primary care HF patients and its impact on the study endpoints will be analysed. In a first step we will compare quality of life, hospitalisation and mortality after a 1-year follow-up period between HF patients with depression/anxiety (P+/+ and P+/−) and those without (P−/−).

In the second step we will compare quality of life, hospitalisation and mortality after a 1-year follow-up period between HF patients with depression and/or anxiety recognized by their GP (P+/+) and those with depression and/or anxiety not recognized (P+/−). We will perform multivariate regression models taking the confounding effects (e.g. comorbidity, sociodemographics, type of treatment for depression/anxiety and heart failure severity) into account.

In a third step we will compare several types of treatment for psychosocial risk factors and their potential effects on quality of life, hospitalisation and mortality after a 1-year follow-up period.

We will compare the information concerning the treatment of psychosocial risk factors gathered from patients with that gathered from GPs to evaluate potential differences (e.g. due to treatment initiated by other healthcare providers than the GP). We will re-run the analyses of the third step for information gathered from patients and for information gathered from GPs separately.

For binary outcomes (hospitalization, survival after 1 year), chi-squared tests will be used. For continuous outcomes (quality of life, survival time), t-tests or non-parametric rank tests will be used. Multivariate linear regression analyses will be performed for the total number of hospitalized days, Cox regression and Kaplan-Meier curves for time to hospitalization survival time. Multivariate linear regression will be used for quality of life.

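### The stated minimum of 118 P−/− patients for 80% power does not agree with the plan's own 504/168 calculation; it is a minor correction, and planned power is not at risk

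*Protocol article*

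**What the plan says.** The section on sample size calculation in the protocol article makes two power statements.

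- **Recognized versus unrecognized.** The aim is "a minimum power of 80% to detect a minimum difference of at least any 5 points" on the EQ-VAS at alpha 0.05. From this the plan derives a total of 672 P+ patients, split into two groups: "of whom 504 have depression and/or anxiety recognized by their GP (P+/+) and 168 with depression and/or anxiety not recognized".
- **The group without depression or anxiety (P−/−).** The plan draws 2,370 such patients and expects 2,015 in the analysis after 15% loss. It adds: "A minimum number of 118 patients at the follow-up assessment would already provide a power of 80% to detect differences between the groups". The sentence goes on to name all three groups and the same 5-point difference, again with alpha 0.05.

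The second statement stands in the paragraph on the P−/− sample, so 118 reads as a number of P−/− patients. Neither statement gives an SD, the sidedness of the test or the test itself.

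Two other places bear on the point. The data analysis section specifies a first step that sets all P+ patients together against P−/−, and a second step comparing P+/+ with P+/−. The quality assurance section says: "The 75% of eligible patients in the observation group 3 exceed the number required by the power calculation".

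**The concern.** Both statements use the same power, difference and alpha. If 80% power needs 504 patients in one group and 168 in the other, then a comparison with only 118 in one group should not reach it while the SD and the test stay the same.

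What is at stake is how a stated figure is read. Set against 2,015 planned patients, a floor of 118 suggests a margin of about 17-fold (2,015/118 = 17.1). With the figures below, the margin is about 13-fold for the comparison with all P+ patients (2,015/155 = 13.0) and about 4-fold for P−/− versus P+/− (2,015/504 = 4.0).

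**Working it through.** **Inputs from the sample size section:** difference 5 points, power 80%, alpha 0.05; 504 P+/+, 168 P+/−, together 672; claimed minimum 118 P−/−; planned 2,015 P−/− at follow-up.

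**Assumptions, not stated in the document:** two-sided test, two-group comparison of means, same SD in all groups.

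**Step 1. Reproduce 504/168.** With multiplier 1.960 + 0.842 = 2.802, the SD that gives 80% power is

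SD = 5 / [2.802 × √(1/504 + 1/168)] = 20.03.

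At SD 20 the noncentral-t power of 504 versus 168 is 80.0%. The plan's figure therefore reproduces at an SD of about 20.

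**Step 2. Compare the two statements without using the SD's value.** At a common SD, two-group power depends on the effective size n₁n₂/(n₁+n₂).

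- For 504 and 168 it is 504 × 168 / 672 = 126.
- With 118 in one group it is always below 118, however large the other group.

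So if 126 is what 80% requires, 118 cannot reach it against any comparator. This step does not need to know the SD, but it does need the SD to be equal across groups and the test to be the same.

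**Step 3. Power with 118 P−/− patients** (SD 20, two-sided 0.05, noncentral t):

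| Comparator | Effective size | Power |
|---|---|---|
| P+/− (168) | 69.3 | 54.6% |
| P+/+ (504) | 95.6 | 68.5% |
| All P+ (672) | 100.4 | 70.6% |
| Unlimited | 118 | 77.5% |

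**Step 4. P−/− patients needed for 80%.** Solve 1/n + 1/m = 1/126 for n, where m is the comparator's size:

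- against all P+ (m = 672): n = 155.1, about 155
- against P+/+ (m = 504): n = 168
- against P+/− (m = 168): n = 504

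**Step 5. Power with the planned 2,015** (SD 20): 87.5% against P+/−, 99.9% against P+/+, and above 99.9% against all P+.

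**Step 6. Could another common SD reconcile the figures?** For 118 to give 80%, the SD would have to be 14.9 (against 168), 17.5 (against 504) or 17.9 (against 672). At those SDs, 504/168 would have 97%, 90% or 88% power, so it would no longer be the number needed for 80%.

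**The case against.** **Unequal SDs.** The result assumes a common SD, and the document states none. If the SD is 20 in P+ but smaller in P−/−, 118 can reach about 80%: at a P−/− SD of 17.5 against all P+, or 16.8 against P+/+ (normal approximation). A somewhat smaller spread in patients without depression or anxiety is possible. This stands as a limit on the power figures, which are conditional. It does not rescue the P+/− contrast, where the P−/− SD would have to be 9.7.

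**A one-sided test.** At SD 20, 118 versus 672 gives 80.4% one-sided. But 504/168 would then have 87.7%, so the two figures would rest on different tests under the same stated alpha. It would also cover only the comparison with all P+ patients.

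**A three-group test.** The sentence names three groups, so a global test may be meant. With 504/168/118 and SD 20, a one-way ANOVA has 60% power if only P−/− differs by 5 points, and 45% to 86% over the patterns tried in which the means span 5 points. It passes 80% only when P+/+ differs from both other groups. If every pair differs by at least 5 points, power is 97%. No such test is described for this figure.

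**Which contrast counts.** The data analysis section specifies all P+ against P−/−, and then P+/+ against P+/−. It specifies no separate test of P−/− against P+/−, although the endpoints section announces comparisons among the three groups. This stands: 504 should not be presented as the single correct minimum.

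**A reading the document does not support.** A reader might infer that group 3 was sized on the wrong floor and could be cut towards 118. The article says instead that the larger number serves quality assurance, so that GPs do not notice the focus on depression and anxiety. It fixes 75% of these patients per practice and a 1:3 ratio in each interview. The statement that group 3 exceeds the power requirement also remains true at 155, 168 or 504.

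**Conclusion.** The concern holds as an inconsistency between two stated figures. Under a common SD of about 20 (implied by 504/168, not stated) and the same two-sided two-group test, 118 P−/− patients give about 71% power against all P+ patients, 68% against P+/+ and 55% against P+/−, not 80%. The ways out are unstated assumptions, and none yields 80% for all the comparisons that the sentence covers.

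The weight is small. It would be too strong to call 55% to 71% the true power of 118, because those figures depend on the equal-SD assumption. It would also be wrong to conclude that the study is underpowered: the planned 2,015 exceeds every corrected minimum, and the 504/168 comparison of recognized with unrecognized patients is untouched. This is a minor correction of one figure.

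**What to change.** In the sample size section, replace 118 with the minimum for a named contrast:

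- about 155 P−/− patients at follow-up for the first-step comparison with all P+ patients;
- about 168 against P+/+;
- about 504 if P−/− versus P+/− is also to have 80% power.

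State the SD, sidedness and test behind both this figure and 504/168. If 118 came from a different SD or test, say so and give it. Add that the planned 2,015 gives about 88% power against P+/− and over 99% against P+/+ or all P+ patients, at SD 20.

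The cost is a few sentences of text. No extra patients or interviews are needed, and the statements that group 3 exceeds the power requirement can stay.

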### Quality assurance

The study is centrally coordinated by the study center Hamburg. All processes regarding the recruitment of GP practices and patients will be parallelized between both recruiting centers. To avoid selection bias, patients with heart failure are selected electronically from the medical records. We use validated instruments for the assessment of baseline and follow-up characteristics. All study staff conducting telephone interviews have been trained. All interviewers are blind regarding the group the patient has been allocated to.

For the data collection from GPs, depression and anxiety is offered in a full list of other potential comorbidities to minimise social desirability bias and to mask the focus on anxiety and depression. Additionally, the GP is interviewed regarding patients with and without depression and/or anxiety. The 75% of eligible patients in the observation group 3 exceed the number required by the power calculation and are suggested to be sufficient to detract from the focus on patients with depression and anxiety. Questionnaires are electronically imported into the database. All import data is double-checked before analysis. Analyses are performed anonymously.

### Data protection

All patients automatically receive a pseudonym which is printed on the consent form included in the study information they obtain. The data of the consent form is entered into a password protected database which is secured on an additional password protected USB stick stored in a lockable cabinet together with the consent forms.

All data assessed in the baseline and follow-up assessment is documented pseudonymously. The data is electronically entered in a local password-secured database. As soon as the data entry of the follow-up assessment is completed the allocation key will be deleted and all data will be anonymous.

### Description of risks

It is not expected that the participation in the study will expose the patients to any risks.

### Ethics approval

The study is conducted in compliance with the Declaration of Helsinki. The study protocol was approved by the local Ethics Committees (Medical Association of Hamburg, Approval No. PV3889; Ethics Committee of the Medical Faculty of the University of Würzburg, Approval No. 125/12, Ethics Committee at the University of Göttingen Medical Center, Approval No. 19/8/11).

### Data analysis

The prevalence of comorbidities in patients with HF and difficulties in the treatment of patients with HF will be analyzed by descriptive statistics. The prevalence of recognition/non-recognition of psychosocial risk factors in primary care HF patients and its impact on the study endpoints will be analysed. In a first step we will compare quality of life, hospitalisation and mortality after a 1-year follow-up period between HF patients with depression/anxiety (P+/+ and P+/−) and those without (P−/−).

In the second step we will compare quality of life, hospitalisation and mortality after a 1-year follow-up period between HF patients with depression and/or anxiety recognized by their GP (P+/+) and those with depression and/or anxiety not recognized (P+/−). We will perform multivariate regression models taking the confounding effects (e.g. comorbidity, sociodemographics, type of treatment for depression/anxiety and heart failure severity) into account.

In a third step we will compare several types of treatment for psychosocial risk factors and their potential effects on quality of life, hospitalisation and mortality after a 1-year follow-up period.

We will compare the information concerning the treatment of psychosocial risk factors gathered from patients with that gathered from GPs to evaluate potential differences (e.g. due to treatment initiated by other healthcare providers than the GP). We will re-run the analyses of the third step for information gathered from patients and for information gathered from GPs separately.

For binary outcomes (hospitalization, survival after 1 year), chi-squared tests will be used. For continuous outcomes (quality of life, survival time), t-tests or non-parametric rank tests will be used. Multivariate linear regression analyses will be performed for the total number of hospitalized days, Cox regression and Kaplan-Meier curves for time to hospitalization survival time. Multivariate linear regression will be used for quality of life.

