### Psychosocial risk factors

Various studies established the important influence of psychosocial factors on the course and prognosis of HF patients [4,5]. Depression affects 20–40% of patients with HF [6] and is 4–5 times more common in HF than in the general population [7]. Depressive symptoms are associated with a 2–3 fold increased mortality risk and were shown to act independently of biological (classical) risk factors [8,9]. Symptoms of anxiety are reported for 38-70% of patients with congestive heart failure [10].

For this reason national and international HF guidelines recommend the regular assessment of depression [11-15] and anxiety [11,12,15] in heart failure patients. However, even though recent evidence suggests that patients screened positive for depression have an increased risk for hospitalization, emergency department visits and mortality [16,17], there is no data available on the transformation of these recommendations into routine care of HF patients.

Different aspects of psychosocial health (e.g. depression, anxiety, social support) are highly interrelated. It is still unclear which factor or component may independently affect the prognosis of HF patients [5]. We are aware of two randomised controlled trials investigating the effects of selective serotonin re-uptake inhibition on morbidity, mortality and mood in depressed patients with HF [18,19]. While the MOOD-HF study is still on-going [18], the SADHART-CHF trial concluded that the lack of effects of sertraline, compared to placebo treatment, may be due to the effect of nurse support within the placebo group, where depression scores improved significantly [19]. However, these trials focus on pharmacological interventions in a tertiary care setting. There are no interventional studies in primary care examining complex interventions such as screening for depression/anxiety (and subsequent treatment initiated by the general practitioner) in HF patients. There are also no studies that examined the effect of recognition and subsequent treatment of depression/anxiety initiated by the general practitioner (GP) once depression and or anxiety have been recognized. Therefore, it will be important to determine whether there is a need for interventional research targeting the effect of treating depression and anxiety on the prognosis of HF in patients with HF in primary care.

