### Recognition of depression and anxiety

In Germany, the recognition rate of depression in the primary care sector has been reported at 74% [20]. Recognition rates among HF patients are likely to be lower because of the symptom overlap of non-specific HF symptoms and symptoms of depression. We are aware of one study investigating recognition rates of depression and anxiety in ambulatory HF patients. This study found that 42.5% of patients screened positive for depression and/or anxiety also had a diagnosis of depression or anxiety in their medical records [21]. However, that study almost exclusively included men (98.7%) and did not investigate the prognostic implication of recognition/treatment of depression/anxiety. Despite the purported clinical relevance of depression and anxiety, no intervention studies investigated the effects of depression and anxiety modification on the prognosis of HF patients in primary care settings. Further, the evidence base to support such trials is slim because so far there is no observational data underlining an association between recognition of depression and anxiety and the depression/anxiety-outcome [22], nor data underlining the cardiovascular outcome in primary care patients with HF [23-25].

As a result of these considerations, the aim of the study is to evaluate the state of psychosocial health care (recognized and unrecognized depression/anxiety and subsequent treatment) and its influence on health related quality of life and prognosis in primary care patients with HF.

Given that the prevalence rates of depression in HF patients vary due to differences in and the threshold levels of the assessment tools used, appropriate cut-off values for self-administered instruments measuring anxiety/ depression in HF patients will be derived in a sub-study.

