## Methods/Design

The study is designed as a multicenter, prospective, observational study investigating 3,950 primary care patients with HF in Germany. The following research questions will be addressed:

● How many patients with HF suffer from depression and/or anxiety?

● How are the recognition rates of depression and/or anxiety by general practitioners (GPs)?

● How often are which measures taken by the GP when depression and/or anxiety are recognized?

● Is there an association between the presence of depression and/or anxiety and quality of life and HF prognosis (hospital admittance and mortality risk)?

● Is there an association between the recognition of present depression/anxiety by the GP and quality of life and HF prognosis (mortality, hospital admissions)?

● Which factors are associated with non-recognition and with failure to initiate adequate interventions (pharmacological or psychotherapeutical)?

● Is there an association between the presence and the recognition of depression/anxiety by the GP and health care aspects (e.g. frequency of contacts with the GP)?

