**GPs: Telephone-interview with insight in the medical record**	
Validation of heart-failure diagnosis	Does the patient have heart failure?/Severity level according to New York Heart Association (NYHA) class/Ejection fraction
Size of practice	Number of GPs in the practice/ Practice type (single practice/practice sharing/group practice)/Number of patients insured by the statutory health insurance per quarter/ Percentage of private patients
Familiarity with the patient	Are you the regular GP of the patient?/How well do you know the patient? (Scale 1 to 10)
Comorbidity	Charlson Comorbidity Index [46]/Which additional diseases does the patient have?
Depression/Anxiety	Does the patient have any symptomatology of depression/anxiety? If yes, please specify/Had the patient any symptomatology of depression/anxiety in the past?
Measures taken if depression/anxiety is recognized	What treatment have you prompted?
Treatment of heart failure	What difficulties have you encountered when treating the heart failure in this patient? Have there been any reasons to deviate from the recommended pharmacological treatment?
Sociodemographic data of the GP	Age/Gender/Years of practice/Speciality/Additional trainings

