## Discussion

This is the first study conducted to investigate the effect of the recognition of depression and anxiety and the subsequently initiated treatment by the GP on the quality of life and the prognosis of heart failure in HF patients in primary care. The results are expected to glean important insights into the care for HF patients in primary care.

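### The step 2 model adjusts the recognition contrast for depression/anxiety treatment, which the protocol itself places after recognition, so the treatment-mediated part of the effect is removed

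*Protocol article*

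**What the plan says.** The Methods/Design section poses the question that step 2 answers: "Is there an association between the recognition of present depression/anxiety by the GP and quality of life and HF prognosis". Under Data analysis, step 2 contrasts P+/+ with P+/− on quality of life, hospitalisation and mortality at one year. It specifies regression models "taking the confounding effects (e.g. comorbidity, sociodemographics, type of treatment for depression/anxiety and heart failure severity) into account".

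Four other places put treatment after recognition:

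- Background, Psychosocial risk factors: the evidence gap includes "subsequent treatment of depression/anxiety initiated by the general practitioner (GP) once depression and or anxiety have been recognized".
- Background, Recognition of depression and anxiety: the aim covers whether the condition is recognised, together with the treatment that follows, and the influence of this care on quality of life and prognosis.
- Discussion, opening paragraph: the study is described as the first on "the effect of the recognition of depression and anxiety and the subsequently initiated treatment by the GP on the quality of life".
- Table 2, GP interview: the treatment item stands under "Measures taken if depression/anxiety is recognized" and asks "What treatment have you prompted".

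Table 2 also collects medication and psychotherapy use from every patient at baseline. Data analysis acknowledges that providers other than the GP may have started treatment. Step 3 compares treatment types separately.

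**The concern.** A confounder comes before the exposure and affects both exposure and outcome. By the article's own account, GP-initiated treatment comes after recognition and is one way in which recognition could help or harm. That makes it a mediator. Conditioning on a mediator changes the quantity estimated from a total effect to, at best, a direct effect. The Data analysis section does not say that this change is intended.

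The contrast bears on the primary outcome and sets the sample size. If recognition works partly through treatment, the adjusted coefficient is pulled towards the part that does not. The study could then report little or no association because of its covariate list. The Discussion intends to carry the findings into statements on screening and the treatment gap, so the meaning of this coefficient matters.

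**Working it through.** **Inputs from the article (Sample size calculation).** Difference of 5 EQ-VAS points, power 80%, α = 0.05, recognition rate 75% (allocation 3:1), 504 P+/+ and 168 P+/−, total 672.

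**Inputs not in the article.** The SD, the sidedness of the test, the share m of the effect that runs through treatment, and the treatment rates in the two groups. These are assumed below.

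**Step 1: reproduce the plan's figure.** With 3:1 allocation, the smaller group needs

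n = (1 + 1/3) × (1.96 + 0.842)² × SD² / 5².

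With SD 20 and a two-sided test, n = 1.333 × 7.85 × 400 / 25 ≈ 167.4, rounded up to 168. The larger group is 3 × 168 = 504, total 672, as stated. Solving backwards from 168 and 504 gives an SD of 20.03. The planned 80% therefore applies to a total difference of 5 points with SD about 20.

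**Step 2: what adjustment leaves.** In a linear model with a total recognition effect of 5 points, of which a share m runs through treatment, the recognition coefficient after adjustment is 5 × (1 − m).

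Without collinearity, its standard error is 20 × √(1/168 + 1/504) = 1.78. The correlation between recognition and treatment multiplies this by √VIF, where VIF = 1/(1 − r²). As an example, assume 60% are treated if recognised and 10% if not. Overall 0.75 × 0.60 + 0.25 × 0.10 = 47.5% are treated, and

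r² = (0.75 × 0.25 × 0.50)² / (0.75 × 0.25 × 0.475 × 0.525) = 0.188, so VIF = 1.23.

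| Mediated share m | Adjusted coefficient (points) | Power, no SE inflation | Power, 60% v 10% treated |
|---|---|---|---|
| 0 | 5.00 | 80.0% | 71.5% |
| 0.25 | 3.75 | 55.6% | 47.5% |
| 0.50 | 2.50 | 28.9% | 24.4% |
| 0.75 | 1.25 | 10.8% | 9.7% |
| 1 | 0 | 5.0% | 5.0% |

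**Step 3: range over treatment rates.** At m = 0.5, power runs from 27.1% (40% v 10% treated, VIF 1.08) down to 13.7% (90% v 5% treated, VIF 2.71).

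**Step 4: check by simulation.** In 4,000 runs per setting at 60% v 10%, the model without treatment gave a coefficient of about 5.0 and power of 79% to 80% for every m. With treatment in the model and m = 0.5, the mean coefficient was 2.53 and power 24.8%.

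**The case against.** The strongest reply is that treatment here is not only a consequence of recognition. Recognition is the GP's judgement in one baseline interview with the records open, so an antidepressant already on file may itself prompt a positive answer. Patients report treatment at the same baseline, and other providers may have started it. Some treatment may therefore precede recognition and mark severity, which would make it a true confounder. This stands. It is a reason to show the treatment-adjusted model as well, not to make it the main one.

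Other replies carry less weight. The covariate list is introduced as examples, and a fuller analysis plan may exist, but this item is named outright and called a confounder. Unadjusted tests are planned, but in an observational comparison they control nothing. Step 3 compares treatments and does not give back the total recognition effect.

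Four stronger readings are tempting, and the article does not support them:

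- *The main question is adjusted away altogether.* That needs m = 1. At a mediated share of 25% or 50%, 3.75 or 2.5 points remain.
- *Unrecognised patients have no treatment by construction.* This holds only for the GP item. Patients in all groups report treatment, and Data analysis does not say which source enters step 2.
- *Treatment and group are nearly collinear.* The VIF is 1.08 to 2.71 under assumed rates, and the top value needs 90% v 5% treated.
- *The existing questions can isolate treatment that preceded recognition.* Table 2 lists no date of recognition, no treatment start date and no prescriber in the patient item.

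**Conclusion.** The point holds. A variable that the article describes as following recognition, and as part of the effect of interest, is listed as a confounder of recognition. Followed as written, the model removes the treatment-mediated part of the P+/+ versus P+/− difference and does not say so. The planned 80% power therefore does not apply to the adjusted coefficient.

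The direction is clear provided that recognition leads to treatment and treatment affects outcome. The size is not known. The figure of 2.5 points with at most about 29% power rests on an SD of 20, a two-sided test and an assumed one-half mediated share. It illustrates the mechanism and does not forecast the loss.

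**What to change.** In step 2, take treatment type for depression/anxiety out of the main models for quality of life, hospitalisation and mortality. Keep comorbidity, sociodemographics and heart failure severity.

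Report the treatment-adjusted model next to it as a secondary analysis, labelled as a direct-effect analysis, and state whether the patient or the GP item supplies the treatment variable. Where the patient's report differs from the GP's, it can serve instead as a sensitivity analysis for treatment started by other providers.

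The cost is one line of wording plus the label, with no new data. The downside is possible residual confounding in the main model by treatment that preceded recognition. The Table 2 items cannot fully remove this, so both results should be presented and the limitation stated.
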